## **DarDar 2-B Nutrition Study Scientific Protocol**

**1. Summary.** The DarDar 2-B Nutrition Study is a randomized, controlled trial of 9 months of a porridge protein-calorie supplement (PCS) and micronutrient supplement (MNS) vs MNS control alone administered to 96 HIV-infected women from Dar es Salaam, Tanzania in their third trimester who plan to exclusively breastfeed for 6 months. The objective is to determine if a PCS will improve health outcomes in these mothers and their infants. The study design is based on an earlier data-gathering study (DarDar 2-A Nutrition Study) which determined dietary intakes, food preferences and the extent of malnutrition in the target group.

Two central issues underscore the rationale for this study: 1) HIV-infected women have increased nutritional demands and/or deficits which are augmented/exacerbated by pregnancy and lactation, and 2) It is highly beneficial for infants in resource-limited settings to breastfeed, even (and especially) in the setting of maternal HIV infection. We hypothesize that optimized nutrition through provision of a culturally acceptable PCS will result in improved maternal and infant health mediated by improved infant growth, improved lactation, better control of maternal viral replication and maintenance of immune function, reduced infant exposure to maternal virus via breast milk, and enhanced maternal-infant transfer of passively acquired immune factors.

**2. Recruitment and eligibility.** HIV-infected women in their second trimester will be recruited by the DarDar Study Nurse from pre-natal clinics at designated hospitals and dispensaries in Dar es Salaam including, but not limited to, facilities at Mbagala, Temeke, Mwananyamala, and Amana Hospitals to begin the study in their third trimester. The protocol will be explained and signed consent obtained. Eligibility criteria include expected residence in Dar during the duration of breastfeeding, willingness to identify a confidante (friend, spouse or relative), minimum age 18 and plan to exclusively breastfeed. Subjects with defined high risk pregnancy (e.g., diabetes, pre-eclampsia) who are typically seen at speciality clinics at district hospitals will be excluded. Subjects with allergy to components of the PCS will also be excluded.

**3. Baseline studies.** All subjects will be given a standardized interview consisting of HIV medical history, and a standardized nutritional assessment (see Section 11) based on a 24-hour recall; a body composition evaluation (height, weight, 3-site skinfold thickness, circumference of upper arm, waist and hip); and laboratory studies (serum albumin, and CBC). Phlebotomy will be performed for CD4 count, and breast milk will be obtained for analysis. All subjects will receive nutritional counseling for pregnancy and breastfeeding and counseling on the risks and benefits associated with exclusive breastfeeding.

At the end of the baseline visit, each subject will be asked to complete a brief questionnaire known as the Informed Consent Evaluation and Feedback Tool (ICE-FT); this has been developed to improve comprehension of the informed consent process and measure how well subjects understand what the study involves and the risks/benefits of participation.

**4. Randomization and intervention.** A master randomization list will be generated by the Data Center at Dartmouth based on 1:1 assignment to PCS/MNS or MNS alone (control). Eligible subjects will be assigned a study number from the randomization list which will determine their assignment. Subjects in the PCS group will receive a supply of the PCS/MNS; subjects in the MNS group will receive a one month supply of MNS. In addition to the MNS women in both groups will be given a thermos for storing prepared foods.

**5. MNS and PCS.** Composition of the PCS is based on data obtained in Study 2-A. The caloric and protein intakes observed in Study 2-A were compared to recommendations of the World Health Organization (WHO) for pregnant and lactating women with HIV and the respective deficits in kcal/d and gm protein/d calculated. The PCS is formulated to cover the 75th percentile of the average calculated kcal and protein deficits in women from Study 2-A. All subjects will be counseled to continue their regular diets and consume the MNS and/or PCS as an additional supplement.

**MNS during pregnancy and lactation.** The MNS (micronutrient supplement) will be a tablet consisting of the standard Tanzanian Ministry of Health multivitamin (1 RDA) for pregnant and lactating women.

**Iron and folate during pregnancy.** Pregnant subjects should also be receiving 60 mg ferrous sulfate PO once daily and 1 mg folic acid PO once daily for the duration of pregnancy. If they are not then iron and folate will be provided each month by the Study. Subjects will be asked to discontinue other vitamin or mineral supplements they may be taking.

**Porridge Protein Calorie Supplement (PCS).** The PCS, designated “Dar-uji” (uji = Kiswahili for porridge) will be a dry packaged mixture to be cooked with water to prepare the PCS porridge.

**Table 1. Dar-uji protein calorie supplement (PCS)**

|                                                    |                                                                                                    |
|----------------------------------------------------|----------------------------------------------------------------------------------------------------|
| Composition per 250g package                       | DarDar Lishe flour* 100 g
Full cream dried milk 100 g
Sugar 50 g
TOTAL 250 g              |
| Daily serving                                      | 250 gm diluted in 900 mL water, boiled, stored in thermos and divided into 3 between-meal feedings |
| Calories                                           | 1062 kcal per 250 gm (354 kcal per serving x 3)                                                    |
| Protein                                            | 41.7 gm per 250 gm [15.6%] (13.9 gm per serving x 3)                                               |
| Frequency of distribution for study subject        | 15 packets every 2 weeks                                                                           |
| Allowance for each child $\leq$ age 7 in household | 4 packets every 2 weeks (280 kcal/day)                                                             |

\*(maize 50g, soy beans 25g, sorghum flour 12.5g, millet flour 12.5g)

**Distribution and monitoring of PCS.** PCS subjects will visit the study clinic monthly for a new supply of the PCS and will be trained to record their daily consumption on a monitoring form. The form will be reviewed by the research worker at each visit. Current breastfeeding practices will be recorded at each study visit for all subjects. In addition, random home visits will be conducted to assess compliance and food sharing.

**Sharing of PCS.** For each child of age  $\leq$  7 living in the same household as the subject we will provide a child's food supplement of Dar-uji (separate color packaging) equal to approximately 280 kcal/day.

**6. Follow-up.** Mothers (and infants) will have monthly study visits for the duration of the intervention at the DarDar study clinics at the IDC and reimbursed for travel for each visit. Following the 9 month treatment

Scientific Protocol, version 1.1

July 6, 2017

intervention, mothers and infants will be evaluated again after 3 months (= infant month 9 below) and again after another 6 months (= infant month 15 below) for a minimum of 15 months after delivery for all mother-infant pairs. At each visit an interview will be conducted to assess intercurrent illness (e.g. infant diarrhea, maternal mastitis), a physical examination conducted, height and weight recorded and a 24 hour recall and standardized 24 hour nutritional recall performed (see Section 11). Additional studies, as outlined in Table 2 (below) will include maternal phlebotomy for CD4 count, CBC and albumin levels, and breast milk sampling. Infants will be tested for HIV by ELISA at 15 months. Infant height and weight will be monitored at each study visit.

**Table 2: Summary of Study B protocol beginning with baseline (BL) evaluation**

|                               |           | Intervention: PCS + MNS vs MNS alone |           |                       |                            |          |          |          |          |          |          |          |                |
|-------------------------------|-----------|--------------------------------------|-----------|-----------------------|----------------------------|----------|----------|----------|----------|----------|----------|----------|----------------|
|                               |           | 3 rd Trimester            |           |                       | Delivery and breastfeeding |          |          |          |          |          |          |          |                |
| MONTHLY evaluations    | BL | -3                            | -2 | -1a | 0                   | 1 | 2 | 3 | 4 | 5 | 6 | 9 | 15      |
| 24 hour recall         |           |                                      |           |                       |                            |          |          |          |          |          |          |          |                |
| Mother                        | x         | x                                    | x         | x                     | x                          | x        | x        | x        | x        | x        | x        | x        | x              |
| History/physical       |           |                                      |           |                       |                            |          |          |          |          |          |          |          |                |
| Mother b           | x         | x                                    | x         | x                     | x                          | x        | x        | x        | x        | x        | x        | x        | x              |
| Infant                        |           |                                      |           |                       | x                          | x        | x        | x        | x        | x        | x        | x        | x              |
| Infant ultrasound             | x         |                                      |           |                       |                            |          |          |          |          |          |          |          |                |
| Laboratory             |           |                                      |           |                       |                            |          |          |          |          |          |          |          |                |
| Mother                        |           |                                      |           |                       |                            |          |          |          |          |          |          |          |                |
| CBC/albumin                   | x         |                                      |           |                       | x                          |          |          |          |          |          | x        |          |                |
| CD4 T cells                   | x         |                                      |           |                       | x                          |          |          | x        |          |          |          |          |                |
| Store plasma c     | x         |                                      |           |                       |                            |          |          |          |          |          | x        |          |                |
| Breast milk                   |           |                                      |           |                       |                            |          |          |          |          |          |          |          |                |
| • Immune factors c |           |                                      |           |                       | x                          |          |          | x        |          |          |          |          |                |
| • Composition d    |           |                                      |           |                       | x                          |          |          | x        |          |          |          |          |                |
| Infant                        |           |                                      |           |                       |                            |          |          |          |          |          |          |          |                |
| HIV ELISA                     |           |                                      |           |                       |                            |          |          |          |          |          |          |          | x e |

a Number of monthly pre-natal visits will vary from 1-3 depending on how early mother is enrolled in third trimester; when possible the baseline visit (BL) will typically be the same as the -3 visit.

b A physical examination will be conducted and nutritional assessment performed including weight, height, 3-site skinfold thickness (triceps, subscapular and suprailiac) and upper arm, and waist and hip circumference. During pregnancy measurements will include only, height, weight, mid arm circumference and triceps skinfold thickness. Fat free body mass and percent body fat will be calculated from anthropometric measurements using the equations of Durnin et al. Upper arm circumference and triceps skinfold measures will be used to calculate mid-arm muscle circumference or area.

c Pro-inflammatory cytokines IL-6 and IL-8 and sIgA will be measured as described below

dPercentage fat content will be measured by standard creatatocrit.

ePlasma will be frozen and stored for possible additional assays of nutritional, virologic and/or immunologic status.

Scientific Protocol, version 1.1

July 6, 2017

**7. Sample size.** The primary endpoint will be infant weight at 3 months. Our hypothesis is that infants of mothers in the active PCS treatment group will have a median 3 month weight 0.5 kg higher than infants of mothers in the MNS control group. The standard deviation of infant weight at 2 months among HIV infected infants born on the African continent is approximately 0.7 kg (IQR of 4.0 to 4.9kg; Violari NEJM 2008). We plan to enroll 96 women in the third trimester of pregnancy, and randomize 48 to each arm. We anticipate that at least 95% of enrolled mothers will give birth to a live infant who survives to 3 months, and that no more than 5% of these mother-infant pairs will be lost to follow-up. Thus we anticipate obtaining the primary endpoint on 85 infants. This gives us 80% power to detect effects of nutrition on infant weight at 3 months of 0.50 kilograms. (1.1 pounds).

**8. Data analysis.** For the primary endpoint, median infant weight, will be compared between the two groups at 3 months using intention to treat (ITT) methodology. Multivariate analysis will be used to control for variables which differ between PCS and MNS treatment arms at baseline (e.g. maternal CD4 at baseline, infant birth weight). The secondary endpoint will be maternal BMI at the end of the intervention (6 months after infant birth).

The method of generalized estimating equations will be used to accommodate repeated measurements of infant weight during follow-up. The cluster unit is the subject and the correlation structure will be unstructured. In addition weight at other time points (e.g., birth, 6 months) will be compared between the two arms using a t-test.

We will use two methods to assess the influence of on compliance on endpoints. The first will be an as-treated analysis done using proportion of supplements reported taken as the exposure. We will test if this correlates with infant weight at 3 months using linear regression to adjust for any baseline covariates that are associated with proportion compliance. As-treated analyses are observational analyses that are subject to bias. Thus, the second approach will be to conduct an instrumental variable analysis which has the benefit of avoiding selection bias. Instrumental variable analysis (based on randomization) will yield an unbiased estimate of the effect of compliance on infant weight at 3 months. Subgroup analyses will be conducted on women entering the study in the lowest BMI quartile.

Additional exploratory endpoints will be infant development, infant diarrheal disease, maternal CD4, maternal albumin, breast milk composition, and breast milk immunological parameters.

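### The primary comparison of 3-month weight in kg leaves infant sex and exact age at weighing unadjusted: precision is lost, and the contrast would be biased if the arms were weighed at different mean ages

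*Protocol*

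**What the plan says.** Protocol section 7 (Sample size) fixes the endpoint: "The primary endpoint will be infant weight at 3 months". The hypothesis is on the same raw scale, a "median 3 month weight 0.5 kg higher than infants of mothers in the MNS control group", and so is the SD, "approximately 0.7 kg (IQR of 4.0 to 4.9kg"), which the protocol takes from infants aged 2 months.

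Section 8 (Data analysis) gives the comparison: "median infant weight, will be compared between the two groups at 3 months using intention to treat (ITT) methodology". Multivariate adjustment is reserved for variables that differ between the arms at baseline, with maternal CD4 and infant birth weight as examples. Generalized estimating equations are planned for the repeated weights, with no stated role for exact age.

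Month 3 is a column of monthly visits in Table 2, without a window. Infant sex, age in days at weighing and weight-for-age are not mentioned.

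Both arms have monthly visits with travel reimbursed (section 6). What is collected there differs. Section 5 says "PCS subjects will visit the study clinic monthly for a new supply of the PCS", and Table 1 adds packets for young children in the household. Controls receive a one-month tablet supply (section 4).

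**The concern.** Infants of this age gain weight daily, and boys are on average heavier than girls. A raw weight at a nominal visit therefore carries two sources of scatter unrelated to the supplement. Both can be removed with simple data.

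The adjustment rule in section 8 does not remove them. Age at weighing is not a baseline variable, so the rule never selects it. Sex would enter only if it happened to be unbalanced. But the reason to adjust for a prognostic variable is that it predicts the outcome, whether or not the arms differ on it. Birth weight, the infant variable named, says nothing about the day of weighing.

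There is also a conditional risk of bias. Porridge against tablets cannot be concealed, no placebo porridge is described, and the PCS arm has an extra reason to attend. If one arm came later on average, its infants would be older and heavier when weighed. Later control visits would hide part of a true effect; later PCS visits would inflate it. Randomisation does not protect against this, because visit timing follows allocation.

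**Working it through.** **The plan's own figures.** Section 7 says "We plan to enroll 96 women in the third trimester of pregnancy, and randomize 48 to each arm". For attrition it assumes that "at least 95% of enrolled mothers will give birth to a live infant who survives to 3 months"; follow-up losses among those pairs are put at 5% at most.

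- Evaluable infants: 96 × 0.95 × 0.95 = 86.6, against 85 stated. Below I use 85, or 42.5 per arm.
- SD: IQR width 0.9 / 1.349 = 0.667 kg, stated as about 0.7.
- SE of a difference in means: 0.7 × √(2/42.5) = 0.152 kg.
- Power for 0.5 kg, two-sided 0.05 (alpha is not stated, so assumed): Φ(0.5/0.152 − 1.96) = 90.9%, against 80% stated.
- For a comparison of medians under normality (efficiency 2/π): Φ(0.5/0.152 × √(2/π) − 1.96) = 74.8%.

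The stated 80% is not reproduced by either route. That is a separate matter; the figures serve here only as the starting point.

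**Precision.** The documents supply none of the next three inputs; all are assumptions.

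- Boy-girl difference d: 0.4-0.6 kg, middle 0.5, with equal numbers of each sex.
- Gain near 3 months g: 20-30 g/day, middle 25.
- Within-arm SD of age at weighing s: 5-10 days, middle 7.

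Share of variance = [(d/2)² + (g·s)²] / 0.7². Residual SD = √(0.49 − numerator). Equivalent number of infants = 85 / (1 − share).

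| d, g, s | Numerator | Share | Residual SD | Equivalent n | Power, means |
|---|---|---|---|---|---|
| 0.4 kg, 20 g, 5 d | 0.040 + 0.010 = 0.050 | 10% | 0.66 kg | 95 | 93.5% |
| 0.5 kg, 25 g, 7 d | 0.0625 + 0.0306 = 0.0931 | 19% | 0.63 kg | 105 | 95.5% |
| 0.6 kg, 30 g, 10 d | 0.090 + 0.090 = 0.180 | 37% | 0.56 kg | 134 | 98.5% |

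If the comparison stays on medians, the middle case moves power from 74.8% to Φ(0.5/(0.63 × 0.217) × √(2/π) − 1.96) = 83%.

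The table treats the 0.7 kg as already containing both sources of scatter. If age scatter is instead added to it, the unadjusted SD in the middle case is √(0.49 + 0.0306) = 0.72 kg and power for means is 89%. At s = 10 days and 30 g/day these become √(0.49 + 0.09) = 0.76 kg and 86%.

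**Timing.** Shift in the contrast = g × difference in mean age between arms.

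| Difference in mean age | Shift at 20-30 g/day | Share of 0.5 kg |
|---|---|---|
| 1 day | 0.02-0.03 kg | 4-6% |
| 3 days | 0.06-0.09 kg | 12-18% |
| 7 days | 0.14-0.21 kg | 28-42% |

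With SE 0.152 kg, a shift of 0.06 kg towards PCS raises the two-sided type I error from 5% to about 7%, and 0.21 kg raises it to about 28%. Shifts of the same size against PCS cut power for a true 0.5 kg effect (means) from 91% to 83% and 48%. The 7-day rows are illustrations, not predictions.

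**Sex.** Chance imbalance has SD 0.5 × √(2/42.5) = 0.108 in the proportion of boys, or 0.108 × 0.5 = 0.054 kg on the contrast. This is random error, already counted in the SE, and not bias.

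**The case against.** A reader might infer that the primary result is biased by visit timing. The documents do not support that. Both arms follow the same monthly schedule with travel paid, controls also come back for a monthly supply, and infants in both arms are weighed at every visit. No section shows or predicts a lag, and its direction cannot be told. A 7-day lag would be 0.7-1.4 within-arm SDs of age, a large separation on a shared schedule. This objection stands: the bias is a possibility to guard against.

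A reader might also infer that the scatter leaves the trial underpowered. On the stated inputs a comparison of means has about 91% power without any adjustment, so that does not follow.

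Nor must the endpoint become a z-score. Weight in kg at a fixed time is a valid randomised endpoint, and the hypothesis, SD and detectable effect are consistently in kg. A z-score primary would require all of section 7 to be reworked.

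It can be said that covariates and visit windows belong in a statistical analysis plan, which is not at hand. That is partly right: a missing window is no finding. But section 8 does fix an adjustment rule, and that rule selects covariates by baseline imbalance. It excludes age at weighing and admits sex only by accident. Replacing a stated rule with a better one is a protocol matter.

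Finally, age at weighing is a post-randomisation variable and may partly reflect infant illness. This stands as a caution, and is why age by arm should be reported next to the adjusted estimate.

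**Conclusion.** The point holds as a modest improvement to the primary analysis. The protocol compares raw kg at a nominal visit under an adjustment rule that cannot reach age at weighing and reaches sex only by chance. Adjusting for both would cut the variance by about 19% (10-37%) and the SD from 0.70 to about 0.63 kg (0.66-0.56). It would also protect against a shift of 0.02-0.03 kg for each day by which the arms differ in mean age at weighing.

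The facts about the endpoint and the rule are in the protocol. The sizes rest entirely on assumed growth rate, sex difference and spread of visit dates, and on the 0.7 kg already containing that scatter. It cannot be concluded that a timing bias exists or that the trial is too small for a comparison of means.

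**What to change.** Leave section 7 as it is: kg at 3 months, the 0.5 kg hypothesis and the sample size all stand. In section 8, state that the primary comparison includes infant sex and exact age in days at weighing as covariates, chosen in advance and kept whether or not they differ between arms. Linear regression serves for a difference in means, and median regression if the median is kept. Report mean age at weighing by arm, and give the sex-specific weight-for-age z-score at exact age as a supporting analysis.

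The cost is small. The simple two-group comparison becomes a model, and date of birth, sex and visit date must be on the case report form. The protocol does not list the form's fields, so this should be checked. The choice should be fixed before outcome data by arm are seen.

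### The primary comparison is of medians with no test named, and the stated 80% power matches none of the obvious tests: about 90% for means, 89% for a rank-sum test, 72–74% for a direct comparison of medians

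*Protocol*

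**What the plan says.** Protocol Section 7 (Sample size) makes infant weight at 3 months the primary endpoint. Its hypothesis is that infants in the supplement arm "will have a median 3 month weight 0.5 kg higher than infants of mothers in the MNS control group". For variability it gives: "The standard deviation of infant weight at 2 months among HIV infected infants born on the African continent is approximately 0.7 kg", with "IQR of 4.0 to 4.9kg" in support. The plan is to enroll 96 women and "randomize 48 to each arm". It expects "at least 95% of enrolled mothers will give birth to a live infant who survives to 3 months" and at most 5% loss to follow-up, leaving 85 infants and 80% power for 0.50 kg. Alpha, sidedness and the test behind the 80% are not stated.

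Section 8 (Data analysis) repeats the median for the primary comparison: "For the primary endpoint, median infant weight, will be compared between the two groups at 3 months using intention to treat (ITT) methodology". It names no test there. For the same variable it then names GEE for the repeated weights, linear regression for the as-treated analysis at 3 months, and a t-test at other ages: "In addition weight at other time points (e.g., birth, 6 months) will be compared between the two arms using a t-test". The form of the adjusted (multivariate) analysis and of the instrumental-variable model is left open.

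**The concern.** The summary measure that decides the trial is fixed twice as a median, while the methods actually named for infant weight target means. Weight at birth and at 6 months is to be compared by means. Weight at 3 months is to be compared by medians, and no reason is given.

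Two things are at stake. First, the power figure cannot be checked against the primary analysis, because the protocol does not say which analysis it belongs to, and the candidates differ by more than 15 percentage points. Second, for roughly normal data a sample median uses the information less efficiently than a mean (asymptotic relative efficiency 2/π = 0.637). If the text is followed literally, the primary endpoint gets the weakest of the natural comparisons.

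**Working it through.** **Inputs.** From Section 7: difference 0.5 kg; SD 0.7 kg; IQR 4.0 to 4.9 kg; 85 evaluable infants (42.5 per arm). Assumed, because not stated: two-sided 5%, normal weights, equal SD in both arms.

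**Evaluable number.** 96 × 0.95 × 0.95 = 86.6, so the stated 85 is close.

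**SD from the IQR.** Under normality, (4.9 − 4.0)/1.349 = 0.667 kg, which the protocol rounds to about 0.7. Both values are carried forward.

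**Standard errors of the between-arm difference at SD 0.7.**
- Means: 0.7 × √(2/42.5) = 0.152 kg.
- Rank-sum: 0.152 × √(π/3) = 0.155 kg (relative efficiency 0.955).
- Medians: 0.152 × √(π/2) = 0.190 kg (relative efficiency 0.637).

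**Does the stated 80% reproduce?** Large-sample power is Φ(0.5/SE − 1.96).
- Means: 0.5/0.152 = 3.29, power Φ(1.33) = 91%.
- Rank-sum: 0.5/0.155 = 3.22, power Φ(1.26) = 90%.
- Medians: 0.5/0.190 = 2.63, power Φ(0.67) = 75%.

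None of these is 80%. A comparison of means would give 80% only at an SD of about 0.82 kg. The noncentral t on 83 degrees of freedom, with the same efficiency factors, is slightly lower:

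| Comparison | SD 0.7 | SD 0.667 |
|---|---|---|
| Means | 90% | 93% |
| Rank-sum | 89% | 92% |
| Medians | 74% | 78% |

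**Simulation of median procedures** (42 and 43 normal infants per trial, two-sided 5%):

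| Procedure | SD 0.7 | SD 0.667 |
|---|---|---|
| Median test, exact or continuity-corrected | 63% | 67% |
| Median regression | 65% | 72% |
| Difference in medians, bootstrap SE | about 72% | 75–77% |
| Median test, uncorrected | about 79% | about 82% |
| Difference in medians, permutation | 80–82% | 82–85% |

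**Other variants.** A one-sided 5% comparison of medians at SD 0.7 has Φ(2.63 − 1.645) = 84% power (noncentral t 83%). Counting all 96 infants, a two-sided comparison of medians has 79.7%.

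**Sample size for 80% at SD 0.7, two-sided 5%, large-sample formula.** Per arm for means: 2 × [(1.96 + 0.84) × 0.7/0.5]² = 30.8, so 31. Per arm for medians: 30.8 × π/2 = 48.3, so 49. That is 98 evaluable, or 98/(0.95 × 0.95) = 108.6, about 109 enrolled against 96 planned.

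**Margin if the SD is larger.** The SD describes HIV-infected infants at 2 months, not this trial's infants at 3 months. At an assumed 0.8 kg, which is not in the protocol, the noncentral t gives 81% for means, 79% for a rank-sum test and 62% for medians.

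**The case against.** The strongest reply is that no shortfall is established, because no median-specific test is named. A rank-sum test is often reported as a comparison of medians, and it has about 89% power. A one-sided median comparison also clears 80%, and some two-sided median procedures reach about 80%. At the SD implied by the IQR, the large-sample figure for medians is 78.7%, close to the stated value. All of this stands, so the shortfall is conditional on the test, the sidedness and the SD.

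A reader might also infer that the trial was sized for means, since Section 7 supplies an SD. The document does not support that. Under normality an SD is equally the scale input for a median calculation, and the stated 80% lies nearer the median result (75–79%) than the mean result (about 91%).

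A reader might further infer that the primary result will be on a different scale from the supporting analyses and cannot be compared with them. That goes too far. Both are in kilograms, and for symmetric weights the mean and median differences target the same quantity. If the weights were skewed enough to separate the two, the efficiency figures above would no longer apply as given.

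Finally, a SAP may name the test, and a median is a legitimate, outlier-resistant summary. That is fair as to the missing test. It does not cover the choice of median or the 80% claim, both of which this protocol fixes.

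**Conclusion.** The point holds in a limited form. Sections 7 and 8 commit to medians for the deciding comparison, alongside mean-based methods for the same variable, and give a power figure that belongs to no identified test. Under the protocol's SD of 0.7 kg, 85 infants, normal weights and an assumed two-sided 5%, power is about 90% for means, 89% for a rank-sum test and 72–74% for a direct comparison of medians (75–79% at SD 0.667).

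A literal comparison of medians probably misses 80%, by some 1 to 8 points across those ranges. Particular procedures fall lower (63–65%) or reach about 80%. It is not shown that the trial is underpowered, nor that it must lose about a third of its information. Both would require a median-specific test that the protocol does not name. What is shown is that the median is the least efficient of the three natural choices for roughly normal infant weight, and that the stated power cannot be relied on until the test is named.

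**What to change.** In Sections 7 and 8 replace *median* with *mean*. Make the between-arm difference in mean 3-month weight, with its 95% CI, the one analysis that decides the trial. Use either a t-test or linear regression on treatment with prespecified covariates measured before randomization. Infant birth weight, which Section 8 gives as an example covariate, is observed after randomization and would not qualify. Report the Wilcoxon test with the Hodges-Lehmann estimate as a sensitivity analysis. Restate the power (about 90% at SD 0.7 kg with 85 infants, two-sided 5%) with test, alpha and sidedness named.

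The cost is protocol wording only: no additional women and no change in study procedures. The downside is that a mean is somewhat more sensitive to outlying weights, which the sensitivity analysis addresses.

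If the sponsor prefers to keep the median, the protocol should name the procedure, alpha and sidedness and recompute the sample size on that basis. By the large-sample formula this is about 98 evaluable and 109 enrolled at SD 0.7 kg.
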